### Endpoints and Statistical Analysis

2.6

The feasibility sample size of 12 participants with MS was chosen to provide a sufficient dataset to analyze the practicality of implementing a VR‐based intervention combined with a passive orthosis. Accounting for an estimated 20% dropout, the sample size is consistent with methodological recommendations for feasibility studies [46].

#### Primary Endpoint

2.6.1

Feasibility of integrating VR and wearable sensors during gait with the passive orthosis in MS. Feasibility will be assessed based on participant adherence to the protocol, completeness of data collection, safety, and overall acceptability of the intervention.

#### Secondary Endpoints

2.6.2

Descriptive changes and trends in gait and balance parameters across sessions (T1, T2, and follow‐up T3), based on spatiotemporal parameters and clinical test results (2MWT, T25FWT, TUG).Associations between physiological signals, wearable/video‐based kinematic data, and subjective clinical or workload scores.Feasibility of establishing preliminary, proof‐of‐concept ML pipelines for gait [47, 48, 49] and physiological data, focusing on technical performance, data quality, and evaluating pipeline viability to inform future predictive models in adequately powered studies.

Continuous data (e.g., gait parameters, questionnaire scores) will be summarized using descriptive statistics (means, medians, standard deviations). Comparisons between sessions (T1–T2 and T1–T2–T3) will be conducted using paired or nonparametric tests to examine trends and variability in the data. Correlations between clinical scores and sensor/video‐based measures will be determined with Pearson or Spearman coefficients. Associations between physiological signals and subjective workload/motion sickness (NASA‐TLX, IPQ, and SSQ) will also be investigated through correlation analyses. The feasibility of establishing preliminary ML pipelines (e.g., using simpler algorithms like regularized linear models or support vector machines) to explore associations with gait quality and participant well‐being from inertial and physiological data will be evaluated. Although the study includes only 12 participants, each participant is expected to contribute multiple gait trials, with each gait cycle constituting an individual analysis instance for feature extraction and model input. Because these instances are not statistically independent, model evaluation will be performed leave‐one‐subject‐out cross‐validation (LOSO‐CV), ensuring that all gait cycles from a given participant are held out together during testing to prevent data leakage, mitigate potential model overfitting and overly optimistic performance estimates. Given the pilot nature of the study, all ML analyses will remain strictly exploratory and results will be reported using descriptive performance metrics (e.g., balanced accuracy, F1‐score) to demonstrate pipeline feasibility rather than model generalizability.

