### Study Objectives and Overview

1.1

This study explores the feasibility of implementing a monitoring system for gait characterization with a passive orthosis in virtual reality environments simulating real‐life conditions. By integrating wearable sensor data with standard clinical functional scales, we aimed to determine whether this approach provides clinicians with objective insights into patient adaptation and gait trends. Outcomes such as energy expenditure, perceived fatigue, and cognitive load will be quantified through both standardized questionnaires and sensor‐derived gait and physiological measures.

The project will be implemented in two phases. An ambulatory phase will include the repetition of standardized gait tests performed with the passive orthosis supported by VR and wearable inertial sensors in simulated environments. A home‐based phase will focus on the feasibility of ecological monitoring of gait with the passive orthosis and wearable sensors during activities of daily living. The proposed system, which integrates VR and wearable technologies, will be examined in terms of feasibility, usability, and acceptability, while gait‐related data will be collected for purely descriptive purposes to examine variability across conditions and sessions. Spatiotemporal gait parameters, routinely used in clinical practice and captured via inertial sensors, will be collected both during VR sessions and in real‐life contexts to monitor descriptive changes in gait patterns while using the orthosis.

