### Study Objectives

2.2

The primary objective of this study is to investigate the feasibility of a monitoring system designed to test gait performance with a passive walking brace in VR environments that closely reproduce real‐life conditions, specifically assessing the framework's usability and overall acceptability. The system integrates wearable inertial sensors with routinely used functional clinical scales with the goal of determining whether this technological approach can provide clinicians with additional objective information, particularly regarding patients' adaptation to the orthosis and trends in gait parameters.

The secondary objectives include assessing the role of VR in replicating everyday contexts, such as the home, workplace, and public spaces, and examining its potential to enhance adaptation to assistive devices in daily life. The study also aimed to examine user satisfaction and technology acceptance in people with MS through validated questionnaires. Furthermore, we will analyze the feasibility of repeated longitudinal assessments and preliminary trends in gait and balance outcomes over time through a follow‐up session carried out 2 months after the last usage of the proposed system. Another objective is to understand the feasibility of characterizing orthosis‐assisted gait in individuals with MS using data collected from wearable inertial sensors and from video recordings processed through skeletal motion models during ambulatory sessions. Finally, the study will determine the technical feasibility of establishing preliminary, proof‐of‐concept ML pipelines. These exploratory analyses are strictly aimed at evaluating data quality, feature extraction workflows, and pipeline viability, rather than developing generalizable predictive models.

This study is designed as an interventional feasibility study and is not powered to detect clinical efficacy outcomes. Clinical, gait, and physiological measures will therefore be interpreted descriptively and exploratorily.

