Once all 12 participants are enrolled and have completed session T0, the first ambulatory session (T1) will take place. Participants will perform two standardized gait and balance tests in a clinical corridor (i.e., T25FWT and TUG) under four conditions: (i) without ExoBand or VR; (ii) with VR only; (iii) with ExoBand only, and (iv) with both VR and ExoBand. In VR conditions, tests will be conducted within fully immersive environments simulating real‐life contexts (e.g., museum corridor, supermarket aisle, basketball court, park, sidewalk, house corridor). For participants reporting cybersickness at T0, augmented VR will be used instead. If possible, the same virtual environment will be maintained across sessions for consistency, selected based on participant preference or clinician recommendation. Participants will then perform a final gait test, the 2MWT, both with and without the Exoband. The 2MWT will not be conducted in a virtual environment, as the test requires participants to walk over a long distance (20 m) for a prolonged duration (2 min), which is not feasible in VR due to the need for the headset to be connected to a PC via cable. In all conditions, rest periods will be provided between tests, or upon participant request, to prevent fatigue. During each test, physiological parameters will be collected with the EmbracePlus wristband. Spatiotemporal gait data, including step length, stance/swing duration, and walking speed, will be collected using the mTest3 system with inertial sensors attached to the shoe laces and trunk. In VR conditions, the Meta Quest 3 cameras will be used to track participants' body movements and replicate them on a virtual avatar. All trials will also be video recorded with the two GoPro cameras for markerless motion analysis. Before and after each VR and brace condition, the NASA‐TLX questionnaire will be administered to quantify perceived physical and mental workload. At the end of T1, participants will complete the SSQ and the IPQ to record the occurrence of motion sickness and the sense of presence. Additional measurements will include the MusiQoL, BICAMS, MFIS, BBS, and the MSWS‐12. Given the limited sample size (*n* = 12), it will not be possible to divide participants into two separate groups (e.g., VR vs. non‐VR, or Exoband vs. no Exoband). Therefore, a within‐subject design will be adopted, with each participant performing all experimental conditions. To minimize potential carry‐over effects associated with the use of the passive orthosis, conditions involving the walking brace will be performed after those without it. The order of the VR condition (with or without Exoband) relative to the non‐VR condition will follow a simple allocation sequence generated before enrollment, so that half of the participants (*n* = 6) perform the VR condition first and the other half perform the non‐VR condition first.

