
For the following 7 days (Th), home‐based monitoring will be conducted to assess the feasibility of data collection in real‐life conditions, with participants asked to wear the ExoBand brace, mTest3 inertial sensors, and the EmbracePlus wristband for at least 8 h per day. Adherence to device usage and data completeness will be monitored throughout this period. Participants will be asked to keep a digital diary documenting daily activities, sleep–wake cycles, and medication use to contextualize the collected data and explore the feasibility of self‐reported logging.

On day 8, participants will return for session T2, replicating all T1 activities. In addition, they will complete the TSQ‐WT questionnaire to quantify participant satisfaction with wearable devices and the TAM questionnaire to assess technology acceptance after home use.

Two months later, participants will attend a follow‐up session (T3) in which T1 activities will be repeated without VR. This final session will examine the feasibility of repeated measurements over time and provide preliminary observations on potential changes in gait or other outcomes since earlier sessions.

Figure 1 presents a detailed overview of the intervention and the planned duration of each session.

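### The planned session-to-session gait comparisons cannot by themselves separate adaptation to the brace from change shared with unbraced walking; the unbraced walks already collected should be reported beside them

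*Protocol article*

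**What the plan says.** Section 2.2 (Study Objectives) asks whether the system can give clinicians added objective information, "particularly regarding patients' adaptation to the orthosis and trends in gait parameters". Section 1.1 (Study Objectives and Overview) says that spatiotemporal parameters are collected "to monitor descriptive changes in gait patterns while using the orthosis".

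The analysis of change over time is one sentence in section 2.6.2: "Comparisons between sessions (T1–T2 and T1–T2–T3) will be conducted using paired or nonparametric tests to examine trends and variability in the data". It does not name the condition whose walks are compared, and it does not combine brace condition with session. The Abstract mentions exploratory comparisons over both conditions and sessions, but only in general terms.

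Section 2.4 (Study Procedure) sets the data available:

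- **T1:** the T25FWT and TUG are walked in four conditions (brace on or off, VR on or off), and the 2MWT with and without the brace, outside VR.
- **T2:** "On day 8, participants will return for session T2, replicating all T1 activities".
- **T3:** two months later, the T1 activities without VR.
- **Order within a session:** "conditions involving the walking brace will be performed after those without it".

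Section 2.2 adds that the study "is not powered to detect clinical efficacy outcomes" and that gait measures are to be interpreted descriptively.

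**The concern.** Suppose like is compared with like, for example the braced T25FWT at T1 and at T2. The change still has two parts. One is specific to the brace. The other would appear without it: repeated practice of the test, familiarity with the corridor and sensors, and how the participant is on the day. The stated comparison returns the sum. Testing each condition separately leaves this unchanged.

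At stake is how a secondary, descriptive result is read. Section 2.6.2 offers no other analysis of change over time. A reader looking for evidence on adaptation would therefore turn to the braced session change and could credit the brace with ordinary practice. The information needed to judge this is collected at every session but is not tied to the question.

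**Working it through.** **Inputs from the document.** n = 12 (section 2.6: "The feasibility sample size of 12 participants with MS was chosen to provide a sufficient dataset"). Dropout is put at 20%, so 12 × 0.8 = 9.6, or about 10 completers. No significance level, SD, effect size or practice effect is given, so there is no figure of the plan's to reproduce here.

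**Step 1: what each change contains.** Let s be the session effect common to both conditions and a the brace-specific change.

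- (a) braced change = s + a + error
- (b) unbraced change = s + error
- (c) = (a) − (b) = a + error

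The braced change is off by exactly s as a measure of adaptation. The difference removes s, provided s really is the same in both conditions.

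**Step 2: how visible s could be (illustrative).** Assume two-sided 5%, a = 0, and s equal to d SDs of the within-person braced change. The rejection rate of the paired t test is then its power at noncentrality d√n:

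| d | n = 12 | n = 10 |
|---|---|---|
| 0.3 | 16% | 14% |
| 0.5 | 35% | 29% |
| 0.8 | 71% | 62% |

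The difference (c) rejects in about 5% under the same model, but only because the model gives both changes the same mean. Step 4 relaxes that.

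**Step 3: precision of (c).** With equal SDs and correlation ρ between the two changes, SD(c)/SD(a) = √(2 − 2ρ). This is 1.18 at ρ = 0.3, 1.00 at 0.5 and 0.63 at 0.8. At n = 12 the 95% half-width for the braced change is 2.201/√12 = 0.64 SD. For (c) it is 0.75, 0.64 or 0.40 SD respectively.

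**Step 4: where (c) fails.** Unbraced walks always come first. Take a participant who does non-VR before VR. The non-VR unbraced and braced walks are then attempts 1 and 3 at T1, and 5 and 7 at T2. Let practice gain be g(k) at attempt k, with no adaptation and no forgetting. Then (a) = g(7) − g(3), (b) = g(5) − g(1) and (c) = (a) − (b):

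| g(k), assumed | (a) | (b) | (c) |
|---|---|---|---|
| ln k | 1.946 − 1.099 = 0.85 | 1.609 − 0 = 1.61 | −0.76 |
| 1 − exp(−0.5(k−1)) | 0.950 − 0.632 = 0.32 | 0.865 − 0 = 0.86 | −0.55 |
| 1 − exp(−0.1(k−1)) | 0.451 − 0.181 = 0.27 | 0.330 − 0 = 0.33 | −0.06 |

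The true value is zero in each row. When practice flattens quickly, (c) is biased against adaptation by an amount close to, or larger than, the bias of (a) in its favour. When learning is slow, (c) is much the better measure. A constant order effect cancels at T2 − T1; one that differs between sessions does not. At T3 there are no VR walks, so the unbraced and braced walks are adjacent attempts and the spacing differs from T1.

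**Step 5: transfer.** If a week of brace use also improves unbraced walking, (c) subtracts it. With a true braced gain of 1 and an unbraced gain of 0.5, (c) shows 0.5.

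**The case against.** The strongest objection is that the document never says a session change will be called adaptation. Section 2.6.2 gives its purpose as trends and variability. Section 2.2 lists adaptation and gait trends as separate items, under a question about whether the technology is informative. For an endpoint defined as change across sessions, a real session change is a correct result. All of this stands. A reader might infer that the plan commits itself to reporting practice as adaptation, or that such a result would be carried into a larger trial; the text supports neither. The Abstract's mention of conditions also leaves room for a brace contrast, and such detail may be in the full plan.

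It is also fair to say that the rates in step 2 are only t-test power at assumed shifts, and that the unbraced-first order can make the difference misleading in its own right. A reader might infer that the difference is the one brace contrast that the fixed order leaves unbiased. Step 4 shows that this holds only if the order effect is stable, and flattening practice would make it unstable.

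What remains is narrower. Adaptation is something the study says it wants information on, the stated comparison cannot isolate it, and the comparator is already measured.

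**Conclusion.** The point holds as a limit on interpretation and a cheap reporting improvement. A braced session change under section 2.6.2 equals adaptation plus whatever unbraced walking also gains; that is algebra and needs no assumed value. The size of the shared part is unknown. The 14% to 71% range rests on an assumed 5% level, shared shifts of 0.3 to 0.8 SD and zero adaptation, and is not an error rate of this trial. Neither the braced change nor the difference is safe alone: practice pushes the first towards apparent adaptation and can push the second away from it. Shown together, they let a reader judge. The consequence is confined to a secondary, descriptive endpoint.

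**What to change.** In section 2.6.2, for the non-VR T25FWT, TUG and 2MWT, report side by side for T2 − T1 and T3 − T1:

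- (a) the braced change;
- (b) the unbraced change;
- (c) the per-participant difference, (a) minus (b).

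Give each descriptively with a 95% CI. Label (a) and (b) as overall session change including practice, and (c) as the exploratory brace-specific change. State the limits of (c) beside it:

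- it removes only effects common to both conditions;
- because unbraced walks come first, flattening practice or an order effect that differs between sessions, including T3 with no VR walks, can bias it, possibly against adaptation;
- it subtracts any transfer of brace use to unbraced walking.

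The cost is one derived variable and a few sentences, with no new visits or measurements. The statistical downside is a wider interval for (c) when the two changes correlate below 0.5, about 18% wider at 0.3.

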## Abstract

Multiple sclerosis (MS) often leads to significant impairments in gait and mobility. Although walking braces are commonly prescribed, their real‐world effectiveness is limited by insufficient adaptation. Traditional clinical assessments rely on subjective scales and may not fully reflect daily‐life challenges. Immersive virtual reality (VR) and wearable sensors offer promising solutions for ecological monitoring, but their combined use remains unvalidated for orthotic support in MS. This interventional study examines the feasibility of a novel, VR‐based framework designed to support gait assessment with a passive walking brace. Twelve participants with MS will undergo a protocol combining four ambulatory sessions and a week‐long home‐monitoring phase. Standardized gait tests will be performed with and without the brace across both simulated scenarios and real‐world conditions. Multimodal data collected via inertial and physiological wearable sensors will characterize spatiotemporal gait parameters, balance, posture, and physiological responses, alongside standardized clinical scales and subjective questionnaires. Overall feasibility will be evaluated directly through user usability and acceptability, recruitment and retention rates, safety, protocol adherence, and data completeness. Given that this pilot study is not powered to assess clinical efficacy, statistical analysis will focus strictly on descriptive and exploratory comparisons across conditions and sessions. This translational framework aims to establish robust feasibility metrics to support the design of future, larger‐scale controlled trials. Ultimately, these preliminary observations will inform more ecologically valid, personalized rehabilitation strategies to improve the integration of assistive technologies into patients' daily lives.

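### Section 2.6.2 examines descriptive between-session gait changes with hypothesis tests, which measure neither trend nor variability; at 9 to 12 people, estimated paired changes with intervals fit the stated aim better

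*Protocol article*

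**What the plan says.** Three places in the protocol article describe the status of the gait data.

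- Section 1.1 (Study Objectives and Overview): gait-related data "will be collected for purely descriptive purposes to examine variability across conditions and sessions".
- Abstract: "statistical analysis will focus strictly on descriptive and exploratory comparisons across conditions and sessions".
- Section 2.2 (Study Objectives): "Clinical, gait, and physiological measures will therefore be interpreted descriptively and exploratorily". The same paragraph says the study "is not powered to detect clinical efficacy outcomes".

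Section 2.6.2 (Secondary Endpoints) then defines the first secondary endpoint as descriptive changes and trends in gait and balance across T1, T2 and T3. The summaries listed are means, medians and standard deviations. The T1-T2 and T1-T2-T3 comparisons "will be conducted using paired or nonparametric tests to examine trends and variability in the data". Later in the section the machine-learning analyses are confined to exploratory use with descriptive performance metrics. No such sentence is attached to the session comparisons.

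On size, section 2.6 says: "The feasibility sample size of 12 participants with MS was chosen to provide a sufficient dataset", and adds: "Accounting for an estimated 20% dropout". Section 2.7 restricts analyses to available data, without imputation.

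**The concern.** Two things do not fit together. First, the wording in section 1.1 and the endpoint's own label promise description, while the method sentence delivers hypothesis tests. Second, the tests are given a job they cannot do. A p-value says how compatible the data are with no change. It does not say how large a change is, in which direction sessions move, or how much people vary. The variability of change is shown by the SD of the paired differences, and a trend by estimated changes with their uncertainty.

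What is at stake is how the secondary results are read. In a sample this small only large observed changes can reach significance. If attention goes to the significant ones, their size will be overstated on average and some may be chance. The primary feasibility endpoint is not affected.

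**Working it through.** **Inputs.** n = 12 and 20% dropout (section 2.6). Four conditions each for T25FWT and TUG, and two for the 2MWT (section 2.4). T3 without VR (section 2.4). At least four spatiotemporal parameters named for the gait system (section 2.3). Assumptions, because the article gives none: two-sided 0.05 per test, normally distributed paired differences, and true changes of 0.3, 0.5 and 0.8 SD of the differences.

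**The plan's own figure.** There is no power calculation to reproduce. The dropout arithmetic gives 12 × (1 − 0.20) = 9.6, so 9 to 10 people with paired data.

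**Smallest observed change that can be significant** (paired t-test): t(0.975, n−1)/√n.

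- n = 12: 2.201/3.464 = 0.635 SD
- n = 10: 2.262/3.162 = 0.715 SD
- n = 9: 2.306/3 = 0.769 SD

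The same numbers are the half-widths of the 95% confidence interval for the mean change, in units of the observed SD of the change. The true change needed for 80% power is 0.89, 1.00 and 1.07 SD respectively.

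**Power and overstatement among significant results.** Power is from the noncentral t distribution. Overstatement is from 400,000 simulated data sets per setting: the mean absolute change among significant results, divided by the true change.

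| Assumed true change | Power, n=12 | Power, n=9 | Overstatement, n=12 | Overstatement, n=9 |
|---|---|---|---|---|
| 0.3 SD | 16% | 12% | 2.34 | 2.61 |
| 0.5 SD | 35% | 26% | 1.55 | 1.72 |
| 0.8 SD | 71% | 56% | 1.15 | 1.26 |

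**How many tests?** The article does not say. Two bounds:

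- Low: one comparison for each of the three clinical tests, so 3.
- High, if every parameter is tested in every condition. T1-T2 has 4 + 4 + 2 = 10 test-by-condition results, 10 × 4 = 40 spatiotemporal results and 8 repeated scales, in total 58. T1-T2-T3, without VR, has 2 + 2 + 2 = 6 results, 6 × 4 = 24 spatiotemporal results and 6 scales, in total 36.

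**Chance of at least one false positive if nothing changes,** for independent tests: 1 − 0.95^k.

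- k = 3: 14%
- k = 36: 84%
- k = 58: 95%, with 58 × 0.05 = 2.9 false positives expected

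Outcomes from the same people are correlated, which lowers these figures. With a simulated common correlation of 0.7, the chance is 40% for k = 36 and 47% for k = 58.

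**The case against.** The best reply is that the abstract announces exploratory comparisons across sessions and section 2.2 allows exploratory interpretation, so the tests in section 2.6.2 are those comparisons. This largely stands. A reader might infer that the whole article forbids testing, but only section 1.1 uses the purely descriptive wording. The conflict is with that phrase and with the endpoint's label.

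A reader might also infer that chance findings will be carried into the next trial. The documents do not say so. The abstract names feasibility metrics as the support for future design, and no section says that a gait estimate or p-value will size a later trial or select its outcomes. It is a risk to guard against, not a plan.

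Nor does the article establish that a later trial would recruit about a fifth of the people it needs. That follows only from a true change of 0.3 SD at n = 12 (1/2.34² = 0.18). At 0.5 SD the fraction is 1/1.55² = 0.42, and at 0.8 SD it is 1/1.15² = 0.76. A controlled trial would in any case be sized on a difference between groups, not on this uncontrolled change.

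The significance level, multiplicity rules and follow-up contrasts may stand in an analysis plan that is not shown, so their absence is not part of this point.

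Finally, a 95% interval has the same threshold as the t-test, and readers can select on whether it excludes zero. That is true. But the interval shows size and uncertainty for every outcome, which is what a descriptive aim asks for. A strict ban on p-values is a matter of preference.

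**Conclusion.** The point holds in a limited form. The purely descriptive wording in section 1.1 and the descriptive label in section 2.6.2 do not fit the chosen method, and tests do not measure what that sentence asks of them. Only the machine-learning analyses have an explicit exploratory limit in section 2.6.2; the session comparisons rely on the general statement in section 2.2.

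At 9 to 12 people, significance requires an observed change of 0.64 to 0.77 SD. Results picked on that basis would be overstated by about 2.3 to 2.6 times at a true change of 0.3 SD, 1.55 to 1.72 times at 0.5 SD, and 1.15 to 1.26 times at 0.8 SD. These figures rest on the assumed 0.05 level, normal differences and assumed effects. Some chance positives may occur, but how many depends on a test count that the article leaves open, from 3 to several dozen; a large count should not be taken as stated. The matter concerns a secondary endpoint and is cheap to put right.

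**What to change.** In section 2.6.2, replace the testing sentence so that the main between-session result is the paired change for T1-T2, T2-T3 and T1-T3. Compare like-for-like conditions, with the T3 contrasts confined to the non-VR conditions. Report the mean and median change with a 95% confidence interval, and the SD of the change.

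Then either drop the p-values, or state that any reported are exploratory, unadjusted and not to be used to choose outcomes or effect sizes for a later trial. Align the wording of section 1.1 with whichever option is taken.

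The cost is a sentence or two, with the same data and software. The downside is that no significance claims can be made and the intervals will be wide, with a half-width of about 0.64 to 0.77 SD of the change. That width is an honest picture of what 9 to 12 people can show.
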